### Family outcome measures

The Autism Family Experience Questionnaire (AFEQ) [7]. This questionnaire measures broader impact of an intervention on the family. Parent (Cronbach’s alpha 0.85), Family (0.83), Child Development (0.81), Child symptoms (0.79), AFEQ total (0.92) [7].

### Secondary parent outcome measures

Parent self-efficacy [42]: This 15-item self-report questionnaire that rates parental confidence in managing behaviours on a 6-point scale ranging from 0 (no confidence) to 5 (complete confidence).Autism Parenting Stress Index (APSI) [43]. This is a measure of parenting stress specific to core and co-occurring features of autism. The overall APSI scale score demonstrates acceptable internal consistency (Cronbach’s alpha 0.83) and test-retest stability (Cronbach’s alpha 0.88) for parents of children with autism [43]. Psychometric properties are good (e.g. Cronbach’s alpha 0.83).Warwick-Edinburgh Mental Wellbeing Scale (WEMWBS) [44] is a 14-item general population screen of wellbeing and is psychometrically robust with good internal consistency (Cronbach’s alpha 0.89) and test-retest reliability (ICC 0.83).

### Participant timeline

#### Procedures

##### Data collection

Baseline assessment and follow-up measures will be collected by RAs blinded to the outcome of randomisation. RAs are trained to high levels of reliability in all baseline characterisation and outcome measures (see Table 1). All families will be allocated a unique number that will be used to identify them on all paper assessment forms throughout the trial. All data collected on paper will be inputted into a data management system for statistical analysis and all identifying data will be stored securely separately. The Clinical Data Management System (Elsevier’s MACRO) used for this trial is fully compliant with all regulatory frameworks for research of this nature. Patients cannot be identified from eCRFs. The CI or delegated person will monitor completeness and quality of data recording in eCRFs and will correspond regularly with site PIs (or their delegated team member) with the aim of capturing any missing data where possible and ensuring continuous high quality of data. All study data will be treated in accordance with the latest Directive on Good Clinical Practice (2005/28/EC).

**Table 1 Tab1:** Time points at which measures and data are collected

Procedure	Screening	Baseline	Treatment phase	Follow-up		
			Weeks 1–8	Week 10	Week 24	Week 52
Informed consent	X					
Child and parent demographics*	X				X	X
Eligibility	X					
ADOS-2		X				
SRS-2		X				
CGI-I					X	
RBQ-2		X		X	X	X
Teacher RBQ-2		X		X	X	X
Measurement of the target behaviour vignette		X		X	X	X
VABS 3		X			X	
Parent self-efficacy questionnaire		X		X	X	X
Autism Parenting Stress Index		X		X	X	X
WEMWBS		X			X	X
Autism Family Experience Questionnaire		X			X	X
Proxy completed CHU9D		X			X	X
EQ-5D-5L		X			X	X
Resource use questionnaire		X			X	X
Time and travel questionnaire		X				
Randomisation**		X				
Weekly intervention (MRB or Learning About Autism)			X			

*Child demographics to include child age, gender, type of nursery/school, diagnosis, current medications, additional diagnoses, ethnicity and previous intervention exposure

*Parent demographics to include level of education, employment status, family structure, attendance at previous courses or interventions relating to children with a diagnosis of ASD

**Randomisation to take place following completion of baseline assessment

Randomisation will be done through the Sealed Envelope (www.sealedenvelope.com/) web-based randomisation service. Allocation will be by a minimisation scheme instead of stratified randomisation to minimise sample fragmentation because of the number of strata and to avoid accidental imbalance between the MRB group and the LAA group. Child level randomisation was preferred controlling for child level characteristics that could affect the primary outcome; treatment centre, age strata (under 5th birthday, 5th birthday and older), ethnicity, and gender. Each case will be assigned a participant ID number and treatment allocation emailed separately to the clinical leads at each site. The clinical leads will inform the families of the outcome of randomisation and this will also be recorded in the participant’s NHS patient record.

We will collect information about severe adverse events; as well as recording severe adverse events in a standard format, we will include events of special interest particularly relevant to this trial, such as significant changes in family or school situation.

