**Methods:**

The study is a clinical and cost-effectiveness, multi-site randomised controlled trial of the Managing Repetitive Behaviours (MRB) parent group intervention versus a psychoeducation parent group Learning About Autism (LAA) (*n* = 250; 125 intervention/125 psychoeducation; ~ 83/site) for parents of young children aged 3–9 years 11 months with a diagnosis of autism.

All analyses will be done under intention-to-treat principle. The primary outcome at 24 weeks will use generalised estimating equation (GEE) to compare proportion of children with improved RRB between the MRB group and the LAA group. The GEE model will account for the clustering of children by parent groups using exchangeable working correlation. All secondary outcomes will be analysed in a similar way using appropriate distribution and link function.

The economic evaluation will be conducted from the perspective of both NHS costs and family access to local community services. A ‘within trial’ cost-effectiveness analysis with results reported as the incremental cost per additional child achieving at least the target improvement in CGI-I scale at 24 weeks.

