### Statistical analysis

#### Sample size

We plan to approach approximately 325 families and expect to randomise 250 families (125 randomised to each arm). Assuming 5% type I error, 90% power, 10% intra-group correlation and equal allocation ratio, 224 families (an average of 8 families per parent group) are required to detect 20% improvement rate between the MRB intervention and Learning About Autism group at 24 weeks. Allowing for an attrition rate of 12%, 250 families will be randomised. The 10% intra-cluster correlation was based on review of group interventions in education trials [45]. Sample size was calculated in R using n4pros in CRTSize package [46].

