### Analysis plan

A statistical analysis plan will be written and agreed by the Trial Steering Committee and Data Monitoring Committee before any analysis is undertaken. All statistical analyses will be carried out using the latest version of R software [46]. All analyses will be done in accordance with intention-to-treat principle where all children and parent outcomes are analysed as randomised. In accordance with CONSORT statement for non-pharmacological interventions, we will report all participant flow. Data will be summarised by trial arm. N, Mean ± SD, (or median ± IQR if data are skewed), Minimum and Maximum will summarise continuous variables, whereas number and percentages will be used to summarise categorical variables.

The analysis of the primary outcome at 24 weeks will use generalised estimating equations with binomial distribution and logit link. Exchangeable working correlation will be used to account for the clustering of children by parent groups. The continuous secondary outcomes will first be analysed at 24 weeks using a difference-in-difference model based on linear mixed effect model accounting for paired data (at baseline and at 24 weeks) per child and clustering of children by parent groups. The same model will be applied to the data at week 52, which will be analysed as longitudinal data incorporating data at baseline and 24 weeks. All binary or categorical secondary outcomes will be analysed using generalised estimating equations. We will also perform subgroup analysis and safety analysis, sensitivity analysis for missing data and assess the impact of the COVID-19 pandemic on primary and secondary outcomes.

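### The primary GEE as described names none of the minimisation factors; if fitted that way and the factors are prognostic, the test is conservative and may lose power

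*Protocol article*

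**What the plan says.** Protocol article, Data collection (the randomisation text after Table 1): "Allocation will be by a minimisation scheme instead of stratified randomisation". The stated aims are to avoid fragmenting the sample and to prevent accidental imbalance between arms. The factors are introduced thus: "Child level randomisation was preferred controlling for child level characteristics that could affect the primary outcome; treatment centre, age strata". Age is split at the fifth birthday, and ethnicity and gender complete the list. No categories are given for ethnicity.

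Protocol article, Analysis plan: "The analysis of the primary outcome at 24 weeks will use generalised estimating equations with binomial distribution and logit link". Then: "Exchangeable working correlation will be used to account for the clustering of children by parent groups". The Methods paragraph of the Abstract gives the same structure: "The GEE model will account for the clustering of children by parent groups using exchangeable working correlation".

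Neither account names a covariate, and neither says that the model is unadjusted. The Analysis plan section also states: "A statistical analysis plan will be written and agreed by the Trial Steering Committee and Data Monitoring Committee before any analysis is undertaken". That plan is not available here.

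**The concern.** Minimisation keeps the arms similar on centre, age stratum, ethnicity and gender. If those factors predict improvement, the treatment estimate varies less from trial to trial than it would under simple randomisation. A model without the factors does not know this. It leaves their effects in the residual and between-group variation and reports a standard error for a design with more chance imbalance than this one has. The test then rejects less often than 5% under the null and gives away some of the precision that the allocation was meant to secure.

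Centre deserves most attention. Study design has families randomised at each site, and Study setting places the groups in locations across three sites, so parent groups appear to be nested in site. The article does not say so outright, and it does not say whether groups stayed within site once they moved online (COVID-19 addendum). If they are nested, site differences left out of the mean model reappear as correlation within parent groups, which the clustered analysis then penalises.

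**Working it through.** **The plan's own figure.** Inputs from Sample size: a type I error of 5%, power of 90%, an intra-group correlation of 0.10 and 1:1 allocation; a 20% difference, read as 20 percentage points; and the resulting target, "224 families (an average of 8 families per parent group) are required".

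- Design effect = 1 + (8 − 1) × 0.10 = 1.7.
- 224 / 1.7 = 131.8 effective families, about 66 per arm.
- 224 / 8 = 28 parent groups, so 28 − 2 = 26 degrees of freedom for a between-group comparison.
- The control-arm rate is not stated. With a two-sided 5% test, the standard two-proportion formula times 1.7 gives 222 at 5% v 25% (pooled variance) and 224 at 6% v 26% (unpooled). At 30% v 50% it gives 422, and 224 families then have about 65% power.

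None of this involves covariates. It matters here only because the simulations below use control rates of 0.30 to 0.34, so their starting power is below 90%. The missing control rate is a separate matter.

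**The mechanism.** For a continuous outcome with independent observations and perfectly balanced factors explaining a share R² of the variance, the unadjusted two-sided error rate is 2Φ(−1.96/√(1 − R²)). R² = 0.10 gives 2Φ(−2.07) = 3.9%; R² = 0.20 gives 2Φ(−2.19) = 2.8%. This shows the direction only, because it ignores the logit link and the clustering.

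**Simulation of the actual design.** Each scenario had 1000 trials of 224 children in 3 sites, with biased-coin minimisation on the four factors and groups of about 8 nested in site and arm. Each trial was fitted with an exchangeable logit GEE, using bias-reduced robust standard errors and a t reference with 26 df, with and without the four factors.

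Assumed, because the documents give no values: residual ICC of 0.10 on the latent scale, or zero; cluster-specific log odds ratio of 0 or 0.95; and log-odds effects per site step / age / ethnicity / gender of 0.2 each (weak), 0.5 each (moderate), or 1.0/1.0/0.7/0.7 (strong).

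Unadjusted v adjusted, ICC 0.10:

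| Factors | Null rejection | Mean SE ÷ true SD under the null | Power |
|---|---|---|---|
| Weak | 3.7% v 3.1% | 0.373/0.354 = 1.05 v 0.398/0.369 = 1.08 | 67% v 65% |
| Moderate | 2.7% v 4.0% | 0.389/0.346 = 1.12 v 0.404/0.379 = 1.07 | 58% v 62% |
| Strong | 0.7% v 3.9% | 0.434/0.314 = 1.38 v 0.421/0.390 = 1.08 | 34% v 60% |

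With no residual clustering, power was 88% v 88%, 80% v 86% and 42% v 81%. Monte Carlo error is about 0.5 points on null rejection and 1.5 points on each power figure.

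Two cautions on reading the table:

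- The adjusted fits are also conservative, with standard errors 7% to 8% too wide. Part of the excess in the unadjusted column therefore comes from the small-sample correction. In the moderate case the omission accounts for roughly the step from 1.07 to 1.12.
- Adjustment does not simply shrink the standard error of the log odds ratio. In the moderate case with a treatment effect, the standard error goes from 0.380 to 0.396 while the estimate goes from 0.847 to 0.926. The ratio of estimate to standard error rises from 2.23 to 2.34, but the odds ratio moves from exp(0.847) = 2.33 to exp(0.926) = 2.52. These are different estimands. The simulated risk difference is 0.52 − 0.32 = 0.20 in both analyses, since the trials are the same.

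**The case against.** The strongest reply is that this rests on silence. The article is condensed, the Analysis plan section lists no model terms at all (not even treatment), and a separate analysis plan is promised before any analysis. Covariate lists are commonly left to such a plan, and minimising on factors does not contradict describing a GEE without listing covariates. Much of this stands. A reader might infer that the sponsor has chosen an unadjusted primary analysis; the documents do not support that, because nothing excludes the factors and the unseen plan may include them. What remains is that the article fixes the distribution, link, working correlation and cluster unit, and the model built from those elements alone ignores the restricted allocation.

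A reader might also infer that the protocol holds these factors to be prognostic. It says only that they could affect the outcome, and the weak scenario shows that adjustment may then gain nothing.

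Finally, the harm is in the safe direction: a conservative test raises no false-positive concern. That stands, and it limits the seriousness of the point. It does not help a trial that fails to show a real effect.

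**Conclusion.** The point holds in conditional form. The described primary model names no minimisation factor. If it is fitted that way and the factors are prognostic, the standard error is too wide and the test conservative. Under the assumed effects the power lost is nil with weak factors, about 4 points (ICC 0.10) to 6 points (no residual clustering) with moderate factors, and about 25 to 39 points with strong ones. The strong case is an upper illustration, not an expectation.

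These figures rest on the assumed factor effects, control rates of 0.30 to 0.34, and parent groups nested in site. The documents supply neither the effects nor the control rate, and they only suggest the nesting. The finding supports a change of wording that should be made; it does not show that the planned analysis is invalid.

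**What to change.** Before unblinding, state in the analysis plan that:

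- the primary GEE includes the minimisation factors: centre, age stratum as minimised, gender, and ethnicity categorised exactly as in the minimisation. Centre is the minimum;
- the result is reported as a standardised (marginal) risk difference beside the conditional odds ratio, because adjustment changes what the odds ratio estimates and the sample size was planned on a difference in proportions;
- the unadjusted GEE is kept as a sensitivity analysis.

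If the unseen plan already says this, nothing more is needed.

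The cost is small. All four factors are used at allocation, so no new data are required. The model gains at least 2 (centre) + 1 (age) + 1 (gender) + 1 (ethnicity, if two categories) = 5 parameters, and more if ethnicity has further categories. If the factors prove weak, those parameters buy nothing.

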### Data management

A Data Monitoring Committee (DMC) will meet once a year to receive reports on recruitment and severe adverse events. The DMC will evaluate the findings of the internal pilot and submit report to NIHR, independently chaired and with an independent statistician. Severe adverse events, and actions taken, will be logged by the senior trial manager (CTU) and a report presented to DMC. The RA will discuss challenges with data collection with research leads at each site and the core research team. The RAs will be responsible for ongoing review of data completeness and any concerns will be discussed within the core research team, CTU and the Sponsor as appropriate.

Primary, secondary and relevant exploratory and sensitivity analyses of the data will take place by the trial statistician and health economist in collaboration with the Chief Investigator. The senior statistician will independently reproduce the primary analyses whilst still remaining blinded to the intervention groups. The senior statistician will have an overview of the entire analyses and will explicitly check the statistical codes. Other members of the team (e.g. the trial health economist) will also have access to data and will undertake analysis as appropriate and necessary. We have carefully considered the ethical implications in relation to this type of parent group intervention trial and there are no anticipated detrimental issues to participants. There are therefore no planned interim analyses. Any arrangements for other researchers in the general field to have access to the primary data will be negotiated separately and COREC informed.

### Statistical analysis

#### Sample size

We plan to approach approximately 325 families and expect to randomise 250 families (125 randomised to each arm). Assuming 5% type I error, 90% power, 10% intra-group correlation and equal allocation ratio, 224 families (an average of 8 families per parent group) are required to detect 20% improvement rate between the MRB intervention and Learning About Autism group at 24 weeks. Allowing for an attrition rate of 12%, 250 families will be randomised. The 10% intra-cluster correlation was based on review of group interventions in education trials [45]. Sample size was calculated in R using n4pros in CRTSize package [46].

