The Managing Repetitive Behaviours (MRB) parent group intervention and study protocol were developed jointly in partnership with parents of young children with autism initially through two developmental parent groups. The intervention was designed to help parents recognise, understand and manage their child’s RRB [25]. The development work was followed by a pilot feasibility and acceptability randomised controlled trial (RCT). The results of the feasibility and acceptability pilot indicated that the MRB intervention was both acceptable to parents and feasible to deliver through routine clinical services. If effective, this intervention has the potential to extend the range of early interventions available to meet the needs of young children with autism and their families, ensuring best use of therapeutic resources and reducing the risk that challenging RRB persist with significant long-term consequences for the child and family. However, before recommending that this parent group intervention is included within local community early intervention services, a fully powered clinical- and cost-effectiveness RCT is required to rule out harmful effects of the intervention and quantify any benefit. This study is a phase 3 superiority trial, with a parallel group design in which each family is randomised 1:1 to one of the two parent group interventions.

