## Methods and design

### Study design

This study is a UK three-site, two-group RCT. After consent families will be randomised at each site to receive either the 8-week MRB parent group intervention or the 8-week Learning About Autism (LAA) parent group equivalent to best current practice and will act as an attentional control for time and attention. Assessments are administered on entry (baseline) to the trial, at the end of the eight parent group sessions (10 weeks), at 24 weeks primary endpoint and at the 52 weeks follow-up.

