### Learning About Autism (LAA) parent group

LAA is an 8-week manualised parent psychoeducation group that will act as an attentional control. LAA is designed for parents of young children with autism and focuses on understanding what autism is, and provides support for parents of young children with autism. It is designed to be run in the community with professionals who have experience of working with young children with autism and their families, and have been trained by a UK-based autism charity, the National Autistic Society, to deliver the intervention. Each weekly session lasts for approximately 2 h (total duration of group intervention is ~ 16 h).

The groups will offer parents and carers psychoeducation on understanding autism and what that means for their individual child such as helping them understand their child’s social communication difficulties and behaviour in different environments. It will also provide advice and guidance on strategies and approaches for dealing with behaviour problems in young children with ASD. There will be opportunities for mutual support and sharing of ideas with other parents. Thus increasing parents’ and carers’ understanding, confidence and responsiveness to their child’s patterns of communication and interaction. This is equivalent to current best practice. It will not include any specific information about the role and functions of RRB, functional analysis and tailored strategies to manage challenging RRB.

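### 250 randomised does not cover the stated 12% attrition, and the 90% power depends on an LAA response rate that the article does not give

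*Protocol article*

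**What the plan says.** All of the sample-size inputs are in one paragraph, under Sample size in the protocol article:

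- Error rates and clustering: "Assuming 5% type I error, 90% power, 10% intra-group correlation and equal allocation ratio". The source of the correlation is given as "The 10% intra-cluster correlation was based on review of group interventions in education trials".
- Target: "224 families (an average of 8 families per parent group) are required to detect 20% improvement rate", comparing MRB with LAA at 24 weeks.
- Attrition: "Allowing for an attrition rate of 12%, 250 families will be randomised".

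The paragraph gives no response rate for either arm. It does not say whether the test is two-sided, or whether the 20% is an absolute difference. The Background section says "This study is a phase 3 superiority trial, with a parallel group design" and argues that a fully powered trial is needed before the intervention is recommended to services.

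The comparator is described under Study design as "equivalent to best current practice and will act as an attentional control for time and attention". The section on the LAA group adds: "It will also provide advice and guidance on strategies and approaches for dealing with behaviour problems in young children with ASD". The same section says that LAA leaves out RRB-specific content, functional analysis and tailored RRB strategies.

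**The concern.** The attrition step contradicts itself. Taking the stated loss off the stated enrolment does not leave the stated requirement.

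The power statement has a different weakness. For a binary outcome, the sample size for a fixed absolute difference depends strongly on the control rate, because that rate sets the variance. Without it, 90% reads as a property of the design, when it holds only over part of the possible range. If the LAA rate lies outside that part, a true 20-point benefit would be missed more often than the one time in ten that the paragraph implies. A non-significant result could then be taken as stronger evidence against such a benefit than it is.

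**Working it through.** **Inputs from the Sample size section:** alpha 5%; power 90%; ICC 0.10; 8 families per group; 1:1 allocation; 224 analysed (112 per arm); 12% attrition; 250 randomised.

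**Assumptions made here:** two-sided test; 20% read as 20 percentage points absolute; normal approximation with unpooled variance.

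**Attrition (no assumption needed)**

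- 250 × 0.88 = 220, which is 4 short of 224.
- 224 / 0.88 = 254.5, so 255 would be needed.
- 224 × 1.12 = 250.9. The stated 250 is close to this, which suggests multiplying by 1.12 instead of dividing by 0.88.
- 1 − 224/250 = 10.4%, the loss that 250 does cover.

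**Reproducing 224**

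- Design effect = 1 + (8 − 1) × 0.10 = 1.7. Effective size per arm = 112 / 1.7 = 65.9.
- n per arm = (1.960 + 1.282)² × [pc(1 − pc) + pe(1 − pe)] / 0.20² × 1.7, with pc the LAA rate and pe = pc + 0.20.
- At 5% versus 25%: variance sum = 0.0475 + 0.1875 = 0.235, so n = 10.507 × 0.235 / 0.04 × 1.7 = 104.9 per arm. In whole groups of 8 this is 14 groups, or 112 per arm and 224 in total. The plan's figure is reproduced.
- At 6% versus 26%: 111.1 per arm, also 14 groups and 224.

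**Where 90% holds.** Power = Φ(0.20 / √{[pc(1 − pc) + pe(1 − pe)] × 1.7 / 112} − 1.96). Setting this to 0.90 gives pc = 6.1% or 73.9%. Between those values power is below 90%.

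| LAA rate | MRB rate | Power, 224 analysed | Total needed for 90% |
|---|---|---|---|
| 5% | 25% | 92% | 210 (224 in whole groups) |
| 10% | 30% | 84% | 268 |
| 20% | 40% | 73% | 358 |
| 30% | 50% | 67% | 411 |
| 40% | 60% | 65% | 429 |

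The difference detectable with 90% power and 224 analysed is 25.5 points at an LAA rate of 20%, and about 27 points at 30% to 40%.

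**Sensitivity of these results**

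- Pooled variance: the limits become 5.3% and 74.7%; power at LAA 20–40% is 63–71%.
- t reference on 26 df: the limits become 4.8% and 75.2%; power at LAA 20–40% is 62–70%.
- One-sided 5%: the limits become 10.7% and 69.3%; power at LAA 20–40% is 76–82%.
- All 250 analysed (two-sided, unpooled): 77%, 72% and 70% at LAA 20%, 30% and 40%.

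**Power cost of the attrition slip.** With 220 instead of 224 at the same design effect, power falls from 91.8% to 91.3% at LAA 5%, and from 72.8% to 72.0% at LAA 20%.

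**The case against.** The strongest objection is that 224 is a correct answer to a question the article does not fully print. With 5% versus 25%, every stated input reproduces it. This is a condensed article that cites a full Protocol Version 6.0, and the LAA rate may be given there. That stands: the missing rate is not in itself an error.

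A reader might infer that the trial's true power is 65–73%, or that a 20-point benefit would be missed about one time in three. The documents do not support this. LAA rates of 20–40% are illustrative and appear nowhere in the article. A low LAA rate is also arguable, because LAA leaves out RRB-specific content and the article gives no CGI-I cut-off for response.

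A reader might also infer that the clustering inflation was left out, since 224 is close to the unclustered total at an LAA rate of about 24%. This cannot be shown, and the paragraph states an ICC, a group size and a cluster-trial package. A one-sided test at 10% versus 30% gives 224 as well (109.2 per arm, rounding up to 14 groups of 8). So the article does not show which assumptions were used.

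On attrition, the objection is that the slip hardly matters. At 5% versus 25% the total before rounding to whole groups is 210, which 220 still exceeds. If loss shrinks groups from 8 to about 7.04, the design effect falls to about 1.60, and power with 220 at LAA 5% is 92.7%, against 91.8% with 224 at 1.7. That answers the size of the slip. It does not make the sentence correct.

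What the objection leaves untouched is that 90% is printed without its condition. For a two-sided test that condition is an extreme LAA rate, for a comparator that the article presents as active and equivalent to best practice.

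**Conclusion.** The point holds in two parts of different weight.

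- **Attrition: wrong as written.** 250 with 12% loss leaves 220, not 224, and 250 allows for 10.4%. This follows from the stated figures alone. The effect on power is under one point.
- **Power: conditional, but stated without the condition.** For a two-sided 5% test and a 20-point absolute difference, 90% holds only at an LAA rate of about 6% or less, or about 74% or more. Sidedness and the absolute reading are assumptions. A one-sided test widens the range to about 11% or less, or 69% or more, and does not restore 90% at LAA 20–40%.

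The figure 224 is not shown to be an arithmetic error, and no particular LAA rate can be taken from the article. The defect lies in how the calculation is reported, and wording can correct it.

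**What to change.** Leave enrolment at 250 and revise the Sample size paragraph:

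1. Give the LAA and MRB response rates behind 224, say that the 20% is an absolute difference (if it is), and say whether the test is one- or two-sided.
2. Present 90% as conditional on those rates. Add the power at other LAA rates (two-sided, 224 analysed: 84% at 10%, 73% at 20%, 67% at 30%, 65% at 40%), or the difference detectable at 90% (about 25 to 27 points at LAA 20–40%). Label these rates as illustrative.
3. Replace the attrition sentence with one saying that 250 allows for 10.4% attrition and that 12% would leave 220.

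The cost is a change of wording in the protocol or SAP, with no change to recruitment or to the primary analysis. The drawback for the sponsor is that the stated power becomes less favourable.

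### The stated 12% attrition allowance does not fit the other figures: 250 randomised families would leave 220, not the 224 required (minor effect on power)

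*Protocol article*

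**What the plan says.** All the figures are in the Sample size section of the protocol article. The assumptions are listed as "Assuming 5% type I error, 90% power, 10% intra-group correlation and equal allocation ratio". On these, the article says that "224 families (an average of 8 families per parent group) are required to detect 20% improvement rate" between the arms at 24 weeks. The number to be enrolled follows from an allowance for loss: "Allowing for an attrition rate of 12%, 250 families will be randomised". The same section gives the split as 125 per arm, and the abstract repeats 250 and 125 per arm.

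The section does not say how the allowance was applied to 224, or whether the average group size of 8 refers to families randomised or families analysed. No other section gives a different attrition rate or a different required number.

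**The concern.** An attrition allowance should ensure that, if loss occurs at the assumed rate, the required number remains. Here it does not: the assumed loss takes the analysed sample below the number to which the article attaches 90% power.

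The practical consequence lies in monitoring and reporting. If retention is exactly as planned, at 88%, the trial will analyse 220 families against a published requirement of 224. It would then appear to have fallen short although its own retention assumption was met. Anyone comparing observed attrition with the stated allowance would also be using the wrong threshold, because the margin actually built into 250 is 10.4%, not 12%.

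**Working it through.** **Inputs, all from the Sample size section:** 224 families required (112 per arm); attrition 12%; 250 randomised (125 per arm); type I error 5%; power 90%; intra-group correlation 0.10; average of 8 families per group. The section does not say whether the test is one- or two-sided, and two-sided is assumed here.

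**1. Where 250 could come from.**
- Multiplying: 224 × 1.12 = 250.88. This gives 250 if rounded down and 251 if rounded up.
- Dividing by the retained fraction: 224 / 0.88 = 254.5, so 255, or 256 for equal arms. This gives 250 only if cut back to a round number.

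The stated 250 is closest to the multiplicative calculation rounded down, but the article does not state its method.

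**2. What 250 delivers.**
- Retained after 12% loss: 250 × 0.88 = 220, or 110 per arm.
- Shortfall: 224 − 220 = 4 families, and 4 / 224 = 1.8%.
- Attrition that leaves exactly 224: 1 − 224 / 250 = 10.4%.

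**3. Power if the design effect does not change** (the average of 8 describes the analysed groups). The design effect is 1 + (8 − 1) × 0.10 = 1.7 for both 224 and 220. Taking 224 to give 90% power as stated:

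Power at 220 = Φ((1.960 + 1.282) × √(220/224) − 1.960) = Φ(1.253) ≈ 0.895.

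**4. Power if loss shrinks the groups** (the average of 8 describes the groups as randomised).
- Number of groups: 250 / 8 ≈ 31.
- Average analysed per group: 8 × 0.88 = 7.04.
- Design effect: 1 + 6.04 × 0.10 = 1.604.
- Effective sample size: 220 / 1.604 = 137.2, against 224 / 1.7 = 131.8 as planned.
- Power = Φ(3.242 × √(137.2/131.8) − 1.960) ≈ 0.911.

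**5. Check against a direct two-proportion calculation.** The article gives no control-arm rate, so 224 cannot be reproduced uniquely. Reading the effect as 20 percentage points, an assumed 5% against 25% needs 65 per arm before clustering. Multiplying by 1.7 gives 110.5, so 111 per arm and 222 in total, or 224 when rounded up to 28 whole groups of 8. At those rates power is 90.4% with 224 families, 89.9% with 220 at a design effect of 1.7, and about 91.5% with 220 in groups of 7.04. Across assumed control rates from 2% to 40%, going from 224 to 220 at a fixed design effect costs 0.4 to 0.8 percentage points of power.

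**The case against.** The strongest reply is that the gap is too small to matter. The stated 250 is within about 2% of 255, the power cost is under one percentage point, and 224 is itself soft: it depends on an unstated control rate and on an intra-group correlation borrowed from education trials, and it may already include rounding up to whole groups. Recruitment was due to complete on 31/08/2020, before the article appeared, so enrolment would not change. All of this stands and sets the severity. It does not make the printed figures agree: a required number is a minimum, and the stated allowance falls below it.

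Three stronger readings are tempting, and the document supports none of them.

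- A reader might infer that the trial is underpowered. The four-family gap does not show this, since planned power stays at roughly 90% in either case. Whether 224 is itself adequate is a separate question.
- A reader might infer that the sample size, attrition and power cannot all be true together. They can: if families are lost from groups that started at 8, then 250 randomised with 12% loss gives about 91% power. Only the retained count of 224 fails.
- A reader might state as fact that the allowance was applied by multiplying by 1.12. That is the likeliest explanation, but the article does not say so, and 255 cut to a round number would also give 250.

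**Conclusion.** Wrong as written, at minor severity. That 12% attrition from 250 leaves 220 rather than 224 follows from the article's own figures and needs no outside assumption.

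The size of the consequence depends on two assumptions: that 224 delivers the stated 90% power in a two-sided test, and which group size applies after loss. On these, expected power lies between about 89.5% (design effect 1.7) and about 91% (design effect 1.60). The correction concerns the accuracy of a published figure, not the soundness of the design.

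**What to change.** Restate the allowance in the Sample size section, without enrolling more families, in one of two ways:

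- state that 250 randomised allows for about 10% (10.4%) attrition while retaining 224; or
- keep 12%, state that 220 families are expected to be analysed, and give the power for 220, saying whether the average of 8 families per parent group is before or after loss.

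The cost is one sentence. The first option makes the stated attrition margin slightly smaller. The second gives a power slightly below or slightly above 90%, depending on the group size assumed after loss. Recruitment and analysis are unaffected.
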